### Treatment allocation

Treatment allocation will be in 1:1 ratio. A randomisation sequence will be developed by the trial statistician who is not involved in recruitment using permuted block design using Stata software [39], stratified by disease type (COPD vs ILD). No trial investigators or personnel will have access to the allocation sequence.

### Safety and adverse event reporting

At each study follow up timepoint, the participants are encouraged to mention any problems since the last visit. For all randomised participants all adverse events, irrespective of causality, will be assessed and recorded as per Improving Palliative, Aged and Chronic Care through Clinical Research and Translation Trials Coordination Centre Standard Operating Procedure 5.17 Adverse Event Reporting [49]. The time period includes the time from randomisation, monthly during the intervention period and at the follow-up review. For patients who meet the eligibility criteria and then do not proceed to randomisation, any adverse events detected during that window of time, should also be reported. If an adverse event is the reason that a person does not proceed to randomisation, this should be recorded. All adverse events will be reported in summary to the reviewing HREC and site RGO and will be followed-up until: resolution; condition stabilises; event can be explained; participant is lost to follow-up; or death.

### Statistical analyses

Phase II feasibility and acceptability outcomes will be analysed descriptively. Outcomes from phase II will inform the delivery of phase III. Phase III primary and secondary outcomes will be analysed on intention-to-treat basis using mixed effect linear regression. Participants will be entered as random coefficients, while time, treatment arm and an interaction between them will be entered as fixed terms. Residuals will be visually inspected and if the model is of poor fit, the outcome will be transformed using natural logarithms. The primary outcome will be expressed as the difference in SF-36 at 12 weeks with 95% confidence intervals. If the model remains of poor fit despite the outcome transformation, then mixed effect ordinal logistic model will be used and results will be expressed as odds ratios with 95% confidence intervals. Additional per protocol analysis will be performed using a subgroup of participants who have completed the last visit and have completed at least 8 sessions over 12 weeks.

Multiple exploratory subgroup analyses will be performed, including: sex (female vs male), age group (60 years, 60–70 years, or > 70 years), disease severity (mild-moderate vs severe), disease type (COPD vs ILD), prior psychological disease (present vs absent), breathlessness (mMRC of 2 vs 3 vs 4), and previous pulmonary rehabilitation (yes vs no). Subgroup analysis will be performed by including an interaction term between subgroup and treatment arm in the initial model. Additional analysis will involve the associations between change in the outcome and compliance to intervention and presence of carer in group sessions. These will be performed using linear regression. Outcomes are collected at multiple time-points throughout the study to allow for better missing data imputation, which will be performed within the mixed effects model (using maximum likelihood estimation).

Semi-structured interviewing will continue until sufficient information power is reached [50]. Given the narrow scope of the qualitative analyses, it is anticipated that sufficient information will be attained with a maximum of 15 COPD patients, 15 ILD patients and 15 carers. Each interview will be transcribed verbatim and thematically analysed for perceived patient and carer preferences, barriers, and opportunities based on the approach described by Braun and Clarke [47]. A purposive selection of session recordings will be analysed for patient experiences, actions, behaviours, and responses based on the approach described by Goodson and Vassar [48]. These qualitative outcomes will supplement the quantitative primary and secondary outcomes from phase III.

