**Fig. 1 Fig1:**
[figure not shown]
Study diagram

The online program will be delivered via a teleconferencing platform such as Zoom. Online, group singing sessions will be conducted by a senior music therapist with expertise in singing and delivering an individualised, enjoyable singing repertoire suitable for patients with ALD (Table 1). Singing activities will focus on breathing control and will include a warm-up. Participants will be encouraged to suggest songs. During the 90 minute class, some time will be dedicated to socialisation and group connection. The exact content and structure of the online group singing sessions will be refined during phase II.

**Table 1 Tab1:** SINFONIA music therapy session plan

Stage	Content	Time
Welcome and check in	•Check and provide support for technical issues •Briefly assess participants for comfort level •Identify any issues for consideration during session	5 min
Relaxation	•Relaxation exercise to support comfort and set expectations	5 min
Warm up	•Revision of techniques •Application of techniques to previous session	15 min
Main session (part I)	•Education, practice, and application of targeted breathing and singing techniques	25 min
Break	•Comfort break for bathroom or refreshments	5 min
Main session (part II)	•Application of targeted singing and breathing techniques to participants preferred repertoire	30 min
Reflection	•Reflection on content of session •Suggestions for independent practice	5 min

In addition to attending weekly, guided, online, group singing sessions, participants will be given music CDs, with repertoire and exercises from the guided group singing sessions, to utilise regularly at home. Control arm participants will receive standard care for 12 weeks, with the option to enroll in 12 weeks of guided, online, group singing at the completion of the study period (no data will be collected during this optional period). Participants and their carers will be contacted at 4-week intervals to collect study assessments. The intervention may be discontinued at any time at the participants request or if the site principal investigator deems a participant too unwell to continue. Data will be collected and stored on a REDcap server which is at least as secure as the source. Data will be accessible only by authorised members of the study team and will be stored in accordance with relevant local policies and guidelines to ensure confidentiality.

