Phase III aims to determine whether guided, online group singing has an effect on quality of life with the primary outcome being between arm difference in quality of life (36-item Short Form Survey (SF-36)) measured at 12 weeks (Table 2) [40]. Secondary outcomes measured using between arm differences at the 12-week timepoint include effects on: anxiety and depression (Hospital Anxiety and Depression Scale (HADS)) [41], breathlessness (Dyspnoea-12) [42], breathlessness mastery (Chronic Respiratory Disease Questionnaire—Self Administered Standardised mastery subdomain (CRQ-SAS)) [43, 44], exercise tolerance (6 Minute Walk Test (6MWT)) [45], loneliness (University of California Los Angeles Loneliness Scale version 3 Short Form (UCLA-3)) [46], healthcare utilisation (self-report), carer quality of life (SF-36, optional), patient and carer perceptions of group singing (thematic analysis of semi-structured interviews) [47], and social dynamics and interactions (ethnographic observation) [48]. We hypothesise that 12 weeks of online, guided group singing will improve health-related quality of life relative to baseline compared to usual care.

Online, group singing sessions will be attended and/or recorded and reviewed by a member of the study team to conduct ethnographic analyses on the interactions between patients, carers, and singing instructors. Additionally, a purposive sample of up to 15 participants from ILD, COPD, and carer groups will be recruited for semi-structured interviews before, during, and after the intervention period to investigate perceptions of the guided, online, group singing intervention. A related ethics approval has been obtained to allow interviews with eligible participants who elect not to continue with the main study (St Vincents Hospital Melbourne HREC, LRR 111.21).

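### The stated primary model adjusts for neither baseline SF-36 nor the randomisation stratum, so the week-12 difference is less precise than the data allow

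*Protocol article*

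**What the plan says.** The protocol article, Statistical analyses, fixes the method: "Phase III primary and secondary outcomes will be analysed on intention-to-treat basis using mixed effect linear regression". It then lists the terms: "Participants will be entered as random coefficients, while time, treatment arm and an interaction between them will be entered as fixed terms". The result to be reported is also stated: "The primary outcome will be expressed as the difference in SF-36 at 12 weeks with 95% confidence intervals". Missing data are handled by maximum likelihood within this model, and the repeated visits are justified on that ground: "Outcomes are collected at multiple time-points throughout the study to allow for better missing data imputation".

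Assessments are four-weekly (Intervention and data collection): "Participants and their carers will be contacted at 4-week intervals to collect study assessments". The hypothesis in Aims and outcomes is that singing "will improve health-related quality of life relative to baseline compared to usual care", which implies that SF-36 is measured at baseline.

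Treatment allocation, and Intervention and data collection, both say that the permuted-block randomisation is stratified by COPD versus ILD. In Statistical analyses, disease type appears only among the exploratory subgroups.

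**The concern.** The article gives an affirmative list of fixed terms for the primary model, and two terms one would expect are not on it. Baseline SF-36 is normally a strong predictor of week-12 SF-36. Under randomisation the arms share the same expected baseline, so a model that uses this fact gives a tighter estimate of the same treatment effect. A model with time, a free arm effect and their interaction does not use it, and neither does a model of post-baseline visits without a baseline covariate. Disease type was thought prognostic enough to stratify on, but the primary analysis does not reflect the stratification.

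What is at stake is the width of the primary confidence interval. The plan expects to lose 40% of participants, so the precision obtained from those who remain matters.

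**Working it through.** **Inputs from Sample size.** Difference 10 points, SD 16, 80% power, 5% significance, 42 per arm, 40% attrition, 140 in total. Allocation is 1:1.

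**Assumed, because the article does not give them.** The correlation ρ between baseline and week-12 SF-36 (shown for 0.3 to 0.7); equal correlation between all pairs of visits at weeks 0, 4, 8 and 12; the dropout pattern; and the variance explained by disease type.

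**Step 1: reproduce the plan's figures.**
- Normal approximation, two-sided: n = 2 × (16 × (1.960 + 0.842) / 10)² = 40.2, so 41 per arm.
- With the t distribution, power is 0.798 at 41 and 0.808 at 42, so 42 per arm.
- Attrition: 84 / (1 − 0.40) = 140.

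Both stated figures reproduce for an unadjusted comparison of two means. The planned power does not rely on baseline adjustment.

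**Step 2: complete data, 42 per arm.** The variance of the week-12 contrast, relative to the raw difference, is 1 for the raw difference, 2(1 − ρ) for the difference in change, and 1 − ρ² with baseline adjustment. The raw SE is 16 × √(2/42) = 3.49.

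| ρ | raw SE | change SE | adjusted SE |
|---|---|---|---|
| 0.3 | 3.49 | 4.13 | 3.33 |
| 0.5 | 3.49 | 3.49 | 3.02 |
| 0.6 | 3.49 | 3.12 | 2.79 |
| 0.7 | 3.49 | 2.70 | 2.49 |

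As a check, the listed model was fitted with categorical time, including baseline as a level, to one simulated complete data set (ρ = 0.6). Its week-12 contrast was 15.146, identical to the raw mean difference. Its SE was 3.23, against 2.67 with baseline as a covariate and 2.54 with a common baseline mean.

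**Step 3: the planned trial, with dropout.** Complete cases overstate the gain, because with dropout the likelihood already draws on earlier visits. Take 70 per arm, with 10, 9 and 9 having their last assessment at baseline, week 4 and week 8, which leaves 42 at week 12. Generalised least squares then gives the SEs below. Power is the normal approximation Φ(10/SE − 1.96).

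| ρ | SE, free arm effect at baseline | SE, common baseline mean | power |
|---|---|---|---|
| 0.3 | 3.39 | 3.29 | 84% vs 86% |
| 0.5 | 3.25 | 2.96 | 87% vs 92% |
| 0.6 | 3.17 | 2.72 | 88% vs 96% |
| 0.7 | 3.07 | 2.41 | 90% vs 99% |

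The SE falls by 1 − 2.96/3.25 = 9% at ρ = 0.5 and by 1 − 2.41/3.07 = 21% at ρ = 0.7. The 95% interval half-width (1.96 × SE) falls from 6.4 to 5.8 points and from 6.0 to 4.7 points respectively.

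**Step 4: the stratum.** If disease type explains a share R² of the variance, including it multiplies the SE by √(1 − R²): 0.995 at 1%, 0.975 at 5% and 0.949 at 10%. Leaving it out at R² = 10% overstates the SE by 1/0.949 − 1, about 5%. For scale, a 10-point COPD/ILD gap with equal numbers gives R² = 5²/256 = 9.8%. With an 80:20 mix it is 0.8 × 0.2 × 100/256 = 6.3%, and the SE is overstated by 3.3%.

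**The case against.** The strongest defence is that a time, arm and interaction model is conventional and valid, that the stated sample size does not depend on adjustment, and that a condensed article may leave covariates to the full protocol or analysis plan. The first two parts stand. The third stands only in part: time coding and contrast statements are often left to a fuller document, but this article does list the fixed terms, and the list omits both.

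A reader might infer four stronger things that the article does not support.

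- **That baseline enters as an unconstrained outcome and contributes nothing.** The article does not say whether baseline is a level of time, or whether time is categorical or linear. No contribution at all is exact only for the marginal week-12 contrast with complete data and categorical time, or if baseline is left out of the model. With dropout, a modelled baseline is partly used. With linear time and complete data at weeks 0, 4, 8 and 12, it gets a weight of 1/4 − (1.5 × 1.5)/5 = −0.2.
- **That chance baseline imbalance passes in full into the result.** In expectation it carries over multiplied by ρ: a 2.5-point imbalance at ρ = 0.6 shifts the raw contrast by 1.5 points. That is sampling variation already inside the standard error.
- **That there are two competing primary estimates.** The hypothesis does speak of improvement relative to baseline. But the abstract, Table 2, Aims and outcomes and Statistical analyses all name the between-arm difference at 12 weeks, and under randomisation the difference in change has the same expected value.
- **That power rises from about 81% to between 90% and 98%.** Those gains belong to 42 complete cases per arm. Step 3 is closer to the planned trial.

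**Conclusion.** The point holds as a loss of precision in a stated method. The listed primary model has no baseline adjustment and no stratum term. The estimate is unbiased, and the 42 per arm and 140 in total stand. Under the assumed dropout, adjustment lowers the SE from about 3.25 to 2.96 at a correlation of 0.5 and from 3.07 to 2.41 at 0.7; at 0.3 the gain is only about 3%. The stratum adds little, at most about 5% of the SE if disease type explains 10% of the variance, and its omission errs on the conservative side. The two gains do not simply add, because baseline SF-36 would absorb much of any COPD/ILD difference. All sizes rest on the correlation, visit structure, dropout pattern and case mix assumed above, and on SF-36 being collected at baseline, as the hypothesis implies. This is a free improvement, not a correction of an error that would invalidate the trial.

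**What to change.** State in Statistical analyses that the primary model uses categorical time and one of two forms: a common baseline mean across arms (time and arm-by-post-baseline-visit terms, no arm effect at baseline), or post-baseline visits only with baseline SF-36 as a covariate. Add disease type (COPD/ILD) as a fixed effect. Name the baseline-adjusted arm difference at week 12 as the single primary contrast. Use the same form for the secondary scales, each with its own baseline.

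The cost is a sentence or two, settled before outcome data are seen by arm. It needs no new data, no extra participants and no change to the sample size.

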### Aims and outcomes

Phase II of the trial aims to determine the feasibility and acceptability of guided, online group singing and will collect preliminary data on effectiveness. The primary outcome of feasibility and acceptability will be assessed by the number of participants (and optional carers) that can be recruited, enrolled, and who complete the study within a six-month period (Table 2). Completion will be defined as attendance at a minimum of eight out of 12 sessions over a 12-week period for the intervention arm and completion of the 12-week assessment for the control arm.

**Table 2 Tab2:** Phase II and III primary and secondary outcomes

PHASE II		
Primary outcome	Timepoint	Detail
Feasibility and acceptability	6 months	Number of participants enrolled, randomised, and who complete the program. Completion is defined as attending 8 of 12 singing sessions or completing the week 12 assessment for control arm participants
PHASE III		
Primary outcome	Timepoint	Detail
Quality of life	12 weeks	Between arm difference in SF-36
Secondary outcome	Timepoint	Detail
Anxiety and depression	12 weeks	Between arm difference in HADS
Breathlessness	12 weeks	Between arm difference in Dypnoea-12
Mastery of breathing	12 weeks	Between arm difference in mastery subdomain of CRQ-SAS
Exercise tolerance	12 weeks	Between arm difference in 6MWT
Loneliness	12 weeks	Between arm difference in UCLA-3
Healthcare utilisation	12 weeks	Between arm difference in self-reported healthcare utilisation
Carer quality of life (optional)	12 weeks	Between arm difference in carer SF-36
Patient and carer perceptions of group singing	Baseline, 4-weeks, 12-weeks	Semi-structured interview thematic analysis
Social dynamics and interactions	Throughout intervention	Ethnographic study of group classes

*SF-36* 36-Item Short Form Survey, *HADS* Hospital Anxiety and Depression Scale, *CRQ-SAS* Chronic Respiratory Disease Questionnaire—Self Administered Standardised, *6MWT* 6-Minute Walk Test, *UCLA-3* University of California Los Angeles Loneliness Scale version 3 Short Form

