### Sample size

No formal power calculation was performed for phase II. Participant numbers will be assessed at 6-months to determine feasibility of phase III. For phase III, given a minimally clinically relevant difference in SF-36 of 10 points (SD 16) [31, 35] and assuming 80% power and 5% significance level, at least 42 participants per arm are required. To account for 40% attrition rate, at least 140 participants will be recruited. Due to the rolling nature of the singing groups, the clustering effect is assumed to be minimal, therefore no adjustment for clustering has been performed.

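### The primary effect measure can move from SF-36 points to a log-scale contrast or an odds ratio after a visual residual check, and the trial is sized only on points

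*Protocol article*

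**What the plan says.** Under Aims and outcomes, Phase III has its "primary outcome being between arm difference in quality of life (36-item Short Form Survey (SF-36)) measured at 12 weeks"; Table 2 repeats this as "Between arm difference in SF-36". The Sample size section works on the same scale: a minimally relevant difference of 10 SF-36 points with SD 16, 80% power and a 5% level, giving at least 42 per arm and 140 recruited after 40% attrition.

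The Statistical analyses section then sets this sequence:

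1. Default: "Phase III primary and secondary outcomes will be analysed on intention-to-treat basis using mixed effect linear regression".
2. First fallback, after the residuals have been inspected by eye: "if the model is of poor fit, the outcome will be transformed using natural logarithms".
3. Reporting, stated directly after the log step: "The primary outcome will be expressed as the difference in SF-36 at 12 weeks with 95% confidence intervals".
4. Second fallback, if the transformed model still fits poorly: "then mixed effect ordinal logistic model will be used and results will be expressed as odds ratios with 95% confidence intervals".

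The section does not say how a log-scale result would be turned back into points, or whether a point difference would still be reported if the ordinal model is used.

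**The concern.** A difference in points, a contrast of log scores and an odds ratio are three different quantities, with different null hypotheses and different clinical readings. Under this sequence the data decide which one becomes the trial's primary result. The 10-point threshold that justifies the trial applies to only one of them. If a fallback is triggered, a reader could be left with a ratio or an odds ratio and no direct way to judge whether the benefit reaches the size the trial was designed to find.

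The first fallback is also a one-directional remedy. A log pulls in a long right tail. It lengthens a left tail and has no value at zero, yet the text prescribes it for poor fit of any kind, and for secondary outcomes as well as the primary one.

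**Working it through.** **1. The plan's own figure.** Inputs from the Sample size section: difference 10, SD 16, power 80%, significance level 5% (two-sided assumed). The normal approximation is n per arm = 2 × [16 × (1.960 + 0.842) / 10]² = 40.2, so 41. The t-based calculation gives power 0.798 at 41 and 0.808 at 42, so 42. Attrition: 84 / (1 − 0.40) = 140. Both stated figures reproduce, and both rest entirely on the point scale.

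**2. Points against a ratio.** A contrast of log scores is most naturally read as a ratio of geometric means. The article does not use that term; this is the usual interpretation. As a simple guide, the ratio equivalent to 10 points is (control mean + 10) / control mean. The article gives no control mean, so a range is assumed:

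| Assumed control mean | Ratio equal to 10 points | Points equal to a ratio of 1.25 |
|---|---|---|
| 20 | 1.50 | 5 |
| 40 | 1.25 | 10 |
| 60 | 1.17 | 15 |
| 80 | 1.125 | 20 |

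The same ratio can therefore be half the target difference or twice it.

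**3. The null hypotheses differ.** Assume lognormal scores with mean 50 in both arms and SDs of 16 and 10. The point difference is 0. The ratio of geometric means is √[(1 + (10/50)²) / (1 + (16/50)²)] = √(1.04 / 1.1024) = 0.97, which is not 1.

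**4. Points against an odds ratio.** The standardised target is 10/16 = 0.625. Under a logistic approximation the odds ratio is exp(0.625 × π/√3) = 3.1. That conversion needs the SD and a distributional assumption, so an odds ratio has no direct reading against 10 points.

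**5. What the log does to skew.** The distributions are assumed, with SD about 16:

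| Assumed shape | Skewness, raw | Skewness, after log |
|---|---|---|
| Left-skewed | −0.60 | −1.45 |
| Near-symmetric | 0.01 | −1.61 |
| Right-skewed, bounded | 0.60 | −1.10 |
| Lognormal | 1.26 | about 0 |

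The log repairs the lognormal shape and overcorrects or worsens the others.

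**6. Is the switch needed for valid inference?** In simulations with 42 per arm, scores clipped to 0–100 and a Welch test on raw scores, type I error stayed between 4.7% and 5.7% under left-skewed, right-skewed and floor-bunched data. This is a two-sample stand-in for the repeated-measures model. It indicates that skew of this order does not by itself force a move away from points.

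**The case against.** The strongest defence is that points are the default, the fallbacks are conditional and their order is fixed in advance. The reporting sentence follows the log step directly, so it may mean that log results are to be returned to points. The trial is described as having a blinded analysis, which limits choosing a model by its result. A numeric criterion for poor fit and the handling of zeros are details that an article may leave to the analysis plan.

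Most of this stands. It rules out calling the section a flat contradiction, and the missing criterion is not pressed here. It does not remove the point: blinding protects the choice of model but does not stop the effect measure from changing, and the odds-ratio branch leaves the point scale explicitly.

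Two stronger readings are tempting and are not supported:

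- **That the log step would cost the trial much of its power.** In simulations with zeros set to 1 before taking logs, left-skewed scores gave power of 58–66% on the log scale against 81–82% on raw scores. But the plan re-checks fit after the log and would probably move on to the ordinal model in that case. The figure also depends on an assumed skew and an assumed treatment of zeros. Under right skew the log gained power (90% against 82%). The article gives no SF-36 distribution from which to choose between these cases.
- **That participants would be lost from the primary analysis because their scores are zero.** The article does not show that zeros are to be expected on SF-36. With repeated assessments analysed by maximum likelihood, a zero at one visit would remove that observation and leave the participant's other visits in place. The problem is more plausible for secondary outcomes such as self-reported healthcare utilisation, where having no contacts is a natural value.

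**Conclusion.** The concern holds in a limited form. The article lets the primary effect measure depend on a residual check. The odds-ratio branch, and the log branch unless it is returned to points by a method the text does not give, cannot deliver the primary outcome set under Aims and outcomes or be read against the difference in the Sample size section. This is a stated rule that is badly fixed, not a missing detail.

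Its size is one of interpretation: over assumed control means of 20 to 80, one ratio of 1.25 spans 5 to 20 points around a 10-point target. The limits of the log (right skew only, undefined at zero) are mathematical facts, but their effect on SF-36 is conditional on a distribution the article does not give. No figure for lost power is claimed. The change should be made before the data are analysed.

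**What to change.** Name the linear mixed model on the original SF-36 scale as the sole primary analysis, with the 12-week between-arm difference in points as the sole primary effect measure, whatever the residuals show. If fit is poor, take the 95% confidence interval from robust (sandwich) standard errors or from a bootstrap that resamples participants. Move the log-transformed and ordinal models to labelled sensitivity analyses. For outcomes that can be zero, such as healthcare utilisation, do not rely on an unadjusted log.

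The cost is a change of wording and some efficiency if scores prove strongly right-skewed; the simulated right-skew case above gives the order of that loss. The 42 per arm and 140 total stay as they are, because both were derived on the point scale.

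### The subgroup analysis adds a time-constant subgroup-by-arm term to a repeated-measures model, so it estimates an average over visits, not modification of the week-12 effect

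*Protocol article*

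**What the plan says.** The Statistical analyses section of the protocol article sets out a mixed-effects linear regression for the phase III outcomes: "Participants will be entered as random coefficients, while time, treatment arm and an interaction between them will be entered as fixed terms". The primary result from that model is the SF-36 difference at 12 weeks with its 95% confidence interval. Table 2 and the Aims and outcomes section give the same time-point for the primary outcome and the quantitative secondary outcomes.

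The same section lists seven exploratory subgroup factors: sex, age group, disease severity, disease type, prior psychological disease, mMRC grade and previous pulmonary rehabilitation. The method is one sentence: "Subgroup analysis will be performed by including an interaction term between subgroup and treatment arm in the initial model". The article names no three-way term with time and no week-12 subgroup contrast.

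The Intervention and data collection section has assessments at four-week intervals, and the Statistical analyses section confirms that several time-points enter the model. No baseline covariate is named. The hypothesis in Aims and outcomes is framed as improvement relative to baseline.

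**The concern.** The primary model lets the arm difference change from visit to visit, and the week-12 value is the one reported. The natural subgroup question is whether that week-12 difference varies with, say, disease type. A two-way subgroup-by-arm term cannot answer it. It forces the subgroup difference in arm contrast to be the same at every modelled visit and estimates one pooled value.

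If singing takes weeks to have its effect, early visits pull the pooled value towards zero. If baseline is one of the visits, it contributes a time at which no treatment has been given.

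This matters most for COPD versus ILD. Disease type is the stratification factor, and the Background says there have been no singing trials in ILD internationally. A reader would take the reported interaction as evidence on whether the week-12 benefit differs in ILD, and it would not be that.

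**Working it through.** **The plan's own figure.** The Sample size section uses a 10-point difference, SD 16, 80% power and 5% significance. Taken as two-sided, n per arm = 2 × (1.96 + 0.842)² × 16² / 10² ≈ 40.2, so 41. The t-test version gives 41.17, so 42, as stated. Then 84 / (1 − 0.40) = 140, also as stated. The sample size is not in question; its SD and totals are used below.

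**Inputs from the article:** SD 16; 140 recruited, 84 after attrition; 1:1 allocation; four-weekly assessments.

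**Assumptions, because the article gives no values:** a true subgroup difference of 10 points in the week-12 arm effect; two equal subgroups, so 35 per arm-by-subgroup cell with 140 completers or 21 with 84; complete balanced data; categorical time; within-person correlation ρ of 0.5 or 0.7 (0.3 as a further case).

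**What the planned term estimates.** With a random intercept and balanced data, the expected coefficient is the plain mean of the modification over the modelled visits.

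| Modelled visits | Linear build-up | Full from week 4 | Week 12 only |
|---|---|---|---|
| 0, 4, 8, 12 | 10 × (0 + 1/3 + 2/3 + 1)/4 = 5.0 | 10 × 3/4 = 7.5 | 10/4 = 2.5 |
| 4, 8, 12 | 10 × (1/3 + 2/3 + 1)/3 = 6.7 | 10 | 10/3 = 3.3 |

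The article speaks of random coefficients, which may include a random slope. The average is then unequal and leans to early visits. With assumed intercept variance 154, residual variance 77 and slope variance 50 to 100 (time scaled to 12 weeks), linear build-up gives 3.7 to 2.9 with baseline and 5.8 to 5.2 without. Full effect from week 4 gives 6.3 to 5.6 with baseline and still 10 without.

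So the planned term recovers 10 in only one of these situations: baseline not modelled and modification constant from week 4.

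**Precision (random intercept, visits 0, 4, 8, 12, m per cell).**

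- Planned term: SE = √[4 × 256 × (1 + 3ρ)/4 / m]. With m = 35 this is 4.28 (ρ = 0.5) or 4.76 (ρ = 0.7). With m = 21 it is 5.52 or 6.15.
- Three-way term at week 12 (change from baseline): SE = √[4 × 2 × 256 × (1 − ρ) / m]. With m = 35 this is 5.41 or 4.19. With m = 21 it is 6.98 or 5.41.

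**Power**, about Φ(expected value / SE − 1.96):

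| Completers | ρ | Planned, linear | Planned, full from week 4 | Three-way, either pattern |
|---|---|---|---|---|
| 140 | 0.5 | 21% | 42% | 46% |
| 140 | 0.7 | 18% | 35% | 67% |
| 84 | 0.5 | 15% | 27% | 30% |
| 84 | 0.7 | 13% | 23% | 46% |

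At ρ = 0.3 with 140 completers and full effect from week 4, the planned SE is 3.73 and the three-way SE is 6.40. Power is then 52% against 35%, so the planned term does better.

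A contrast in week-12 level, not change from baseline, has SE = √(4 × 256 / m) whatever ρ is: 5.41 with 140 completers (46%) and 6.98 with 84 (30%).

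**The case against.** The strongest reply is that this is shorthand. The article condenses a fuller protocol that is not shown. In the primary model the treatment effect is carried by time-by-arm, so an interaction with treatment arm could mean letting that whole effect vary by subgroup. That is possible, and the authors may have intended it. But the sentence names both the term and the model it joins, and nothing in the text points to a time component. If a three-way term was meant, the published sentence misdescribes the analysis and needs the same correction.

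Second, an effect averaged over follow-up is a legitimate exploratory quantity, and the article sets no week-12 target specifically for subgroups. This stands in part. Carrying over the week-12 target is an inference, though a natural one, since it is the article's time-point for the primary and all quantitative secondary outcomes. An average chosen on purpose should be declared and should leave out baseline.

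Third, several stronger readings are tempting but not supported:

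- *Baseline is certainly a modelled visit.* The missing baseline covariate and the hypothesis relative to baseline suggest it, but no sentence says so. Without baseline the averaging remains, over weeks 4, 8 and 12, but the dilution by an untreated visit does not.
- *The subgroup effect will be halved.* That needs linear build-up, a random intercept and baseline in the model.
- *Power is always lost.* It is not, as the full-from-week-4 cases show. Figures for 140 completers are also optimistic when the article itself plans for 40% attrition.
- *Chance baseline imbalance makes the test invalid.* A persistent 5-point imbalance between cells, with no true modification, does give a coefficient of 5.0. But under randomisation this is chance variation already counted in the standard error, not systematic bias.

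**Conclusion.** The point holds on the text as written. The stated term yields one time-constant coefficient, a weighted average over the modelled visits, and not modification of the week-12 arm difference. That follows from the form of the model and does not depend on the assumed correlation.

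The size does depend on assumptions. For an assumed 10-point modification at week 12 that is linear or full from week 4, a random-intercept model returns between 5.0 and 10, and random slopes can take it below 4 under linear build-up. The power gap is large under linear build-up, and small or reversed if the effect is full from week 4 and the correlation is 0.5 or lower.

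The consequence is confined to the exploratory subgroup analyses. The primary week-12 estimate, the secondary outcomes and the sample size are untouched. Nor does the correction make the subgroup tests well powered: with 84 completers and two equal subgroups it reaches only 30–46% for a 10-point modification, and age group and mMRC have three levels. The case for the change is that the estimate should match the question. It is worth making before the analysis, but it does not threaten the trial's main conclusion.

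**What to change.** Replace the sentence on subgroup analysis with:

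> *Subgroup effects will be tested by the subgroup-by-arm-by-time interaction (with all lower-order terms), using the week-12 contrast, and reported as subgroup-specific arm differences at week 12 with 95% CI.*

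Also state whether baseline SF-36 is a modelled visit, because that decides which contrast is meant. With baseline as the reference visit, the three-way term at week 12 is modification of the change from baseline. If the first modelled visit is week 4, the three-way term alone would measure change since week 4, so the week-12 contrast must be the sum of the subgroup-by-arm term and the week-12 three-way term. Test and reported estimate should use the same contrast.

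The cost is wording in the analysis plan only. Design, data collection and sample size do not change.
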